#### Data Collection

We will conduct 5 co-design videoconference sessions with each group over 6 months, with a gap of 2 to 3 weeks between each session (Textbox 1; during the periods between the sessions, input from the alternate design team will be synthesized for presentation to the next team and an analysis performed of prior session content). In session 1, we will present the process map generated in phase 1 and a prototype of the current pCGA implementation package. Researchers will facilitate the discussion, maintaining respectful debate among design team members as they identify process changes that will promote the implementation of the pCGA package. The facilitators will focus on solution convergence from session to session. Each design team will participate in sessions independently; however, we will summarize the output from each session and present it to the alternate design team for comment. Each session is expected to last 90 minutes. Sessions will be conducted virtually to promote participation and retention and audio recorded for qualitative analysis. Co-design sessions will be conducted separately for the academic hospital and the community-based hospital.

Outline of the participatory co-design sessions.

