### Phase 3: Pilot Trial of the pCGA Implementation Package

#### Study Design

We will conduct a pretest-posttest pilot study of the implementation package over 10 months, conducted at the clinic level at 2 busy academic medical center surgical subspecialty clinics performing major abdominal surgery (selecting one that does not routinely refer for pCGA in addition to one that does routinely refer). We will collect baseline prepilot data via retrospective chart abstraction from the year before the intervention. After an implementation rollout period of 2 months, postintervention data will be collected over 10 months. Specifically, we will assess outcomes according to the RE-AIM framework [38], using chart abstraction for patient-level data and simple self-reported surveys for the health care professionals. We hypothesize that a user-designed implementation package will improve the reach and adoption of the pCGA compared to the historic baseline.

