##### Health Care Professionals

Consistent with implementation research, health care professionals using the pCGA implementation package are considered study participants [76]. As participants from among the health care professionals who participated in the co-design will be recruited for the pilot trial, they will be familiar with the intervention. Surgeons referring patients from the 2 clinics (n=12) and health care professionals engaged at the pCGA clinic (n=10) will be asked to participate in the pilot.

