##### Intervention

The pCGA implementation package (generated via phase 2) will include a set of implementation strategies [74,75] and an explicit stepwise plan defining the people, tasks, tools or technology, relevant organizational factors, and physical or virtual environment [65] for the pCGA. The implementation package will target systems-level processes to promote pCGA administration before surgery (eg, automating referrals in the electronic medical record, improving patient education materials, or increasing telehealth opportunities).

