## Results

### Overview

We anticipate that this study will take approximately 60 months to complete, from study start-up procedures to the completion of the pilot trial. The 3 phases will take place between June 2023 and March 2028. We expect the results outlined in the following subsections. The study was funded in April 2023. Phase 1 officially started in May 2023 with the first enrollment June 2023. Data collection were completed in February 2024; however, recruitment was extended specifically for vulnerable populations such as underrepresented minority groups. Phase 1 remains open as of August 2024. This action was made due to low recruitment of underrepresented minority groups in an effort to honor the NIH commitment to diversity, equity, inclusion and accessibility. Phase 2 of the study was initiated in May 2024 and remains ongoing in August 2024.

### Phase 1

The results of this phase will include a detailed process map and the corresponding barriers and facilitators as a starting point for system redesign to improve the implementation of the pCGA, specifically expanding reach while maintaining fidelity.

### Phase 2

The results of the participatory co-design sessions at the academic medical center are expected to converge upon an adaptable pCGA implementation package, ready for feasibility and pilot testing (stage IB of the NIH Stage Model). Stakeholder design sessions at the community-based hospital will serve as a template for user-centered implementation of the pCGA at a future date. The results of co-design at the community-based hospital will provide a starting point for understanding the potential generalizability of the implementation package and the extent to which adaptation may be needed to begin implementation at new sites.

### Phase 3

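### Part of the 12-month 'historic' baseline, and possibly all of it, falls during or after co-design with some of the pilot's own professionals, and none of it precedes phase 1

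*Protocol article*

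**What the plan says.** All references are to the protocol article.

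- **Baseline.** Phase 3, Study Design: "We will collect baseline prepilot data via retrospective chart abstraction from the year before the intervention".
- **Post period.** Same section: "After an implementation rollout period of 2 months, postintervention data will be collected over 10 months".
- **Comparison.** Same section: the hypothesis is that the package "will improve the reach and adoption of the pCGA compared to the historic baseline".
- **Where the intervention comes from.** Phase 3, Intervention: "The pCGA implementation package (generated via phase 2) will include a set of implementation strategies".
- **Length of co-design.** The Data Collection section of phase 2 sets out the schedule: "We will conduct 5 co-design videoconference sessions with each group over 6 months, with a gap of 2 to 3 weeks between each session".
- **Status of co-design.** Results, Overview: "Phase 2 of the study was initiated in May 2024 and remains ongoing in August 2024".
- **Start of phase 1.** Same section: "Phase 1 officially started in May 2023 with the first enrollment June 2023".
- **Who takes part.** Phase 3, Health Care Professionals: "participants from among the health care professionals who participated in the co-design will be recruited for the pilot trial". The phase 2 section on health care professionals adds that, at the academic centre, the co-design professionals are those of phase 1. In phase 1, ten referring surgeons are invited to interviews about barriers to and facilitators of adopting the pCGA.

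The article gives no start date for phase 3. The Limitations section does not mention prior study contact during the baseline year.

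**The concern.** The baseline is tied to the intervention date, and the intervention can only follow co-design. The comparison year therefore cannot be free of study activity at the centre where the pilot runs.

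The activity also bears directly on the primary outcomes. Reach is the share of eligible patients referred, and adoption is the share of surgeons who refer. One of the five co-design sessions is devoted to inputs such as referrals, and the strategies sought in phase 2 are those that would raise reach and adoption. Surgeons are eligible as co-designers.

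If that contact raised referral before rollout, the baseline would be too high and the estimated change too small. A pilot meant to supply planning data would then understate what the whole programme of work achieved. The baseline as defined gives no way to see whether this had happened.

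**Working it through.** **Inputs.** Study period April 2023 to March 2028 (Abstract, Methods). Phase 1 start May 2023, phase 2 start May 2024, phase 2 ongoing August 2024 (Results, Overview). Sessions over 6 months (Phase 2, Data Collection). Baseline 12 months, rollout 2 months, post period 10 months (Phase 3, Study Design). Design teams of 7 (Phase 2, Participants). Pilot professionals: 12 surgeons and 10 clinic staff (Phase 3, Health Care Professionals).

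**The plan's own figure.** April 2023 to March 2028 inclusive is 9 + 4 × 12 + 3 = 60 months, which matches the stated duration.

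**Range of start dates.** Let S be the first month of rollout. Co-design was still running in August 2024, so S is September 2024 at the earliest. The pilot takes 2 + 10 = 12 months and must end by March 2028, so S is April 2027 at the latest.

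**Overlap.** I read the baseline as the 12 months immediately before S and take May 2024 as the opening of co-design. Let k be the number of months from May 2024 to S. The number of baseline months during or after co-design is min(12, k). Co-design itself is taken as May to October 2024.

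| S (assumed) | Baseline year | Before co-design | During | After |
|---|---|---|---|---|
| Sep 2024 (extreme lower bound) | Sep 2023–Aug 2024 | 8 | 4 | 0 |
| Nov 2024 (six-month co-design just finished) | Nov 2023–Oct 2024 | 6 | 6 | 0 |
| Jan 2025 | Jan 2024–Dec 2024 | 4 | 6 | 2 |
| May 2025 | May 2024–Apr 2025 | 0 | 6 | 6 |
| Nov 2025 | Nov 2024–Oct 2025 | 0 | 0 | 12 |
| Apr 2027 (latest) | Apr 2026–Mar 2027 | 0 | 0 | 12 |

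The earliest possible baseline month is September 2023, after phase 1 began in May 2023. The minimum of 6 months does not depend on the May 2024 date: a pilot that follows six months of sessions has at least 6 baseline months during or after them.

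**How many professionals.** The article does not say how many co-design surgeons work in the two pilot clinics. If each location has one 7-person professional team (an assumption), co-design covers at most 7/22 = 32% of pilot professionals. It covers at most 7/12 = 58% of surgeons, and only if every member were a pilot-clinic surgeon. The other roles listed for the teams make that unlikely.

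**Effect on the comparison.** The observed difference equals the true difference minus the baseline shift. With an assumed true baseline reach of 30% and post reach of 50%, the true difference is 20 points:

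- shift 0: 20 points observed
- shift 5: 50 − 35 = 15 points
- shift 10: 50 − 40 = 10 points

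To show what might produce such shifts, assume equal surgeon volumes, so that shift = (exposed surgeons ÷ 12) × (rise in their referral) × (share of baseline months exposed). One exposed surgeon with an assumed 20-point rise over the full year gives 1/12 × 20 = 1.7 points. Two with a 30-point rise give 2/12 × 30 = 5.0 points. If only 4 of 12 months are exposed, these fall to 0.6 and 1.7. The article supports none of these rises; they show scale only.

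Adoption moves in coarse steps: one surgeon of 12 counted as an adopter during the baseline year shifts it by 1/12 = 8.3 points, and two by 16.7.

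**The case against.** - **Full overlap is not forced.** A reader might infer that the whole baseline year must lie within or after co-design. The documents do not support that. A start before May 2025 leaves some months before co-design (6 with a November 2024 start, 8 in the extreme case), though all of them lie within the phase 1 period. This stands.
- **The exposed group is a subset.** A reader might take the baseline surgeons and the co-designers to be the same people. A 7-person team with several professions cannot cover 12 surgeons and 10 staff. This stands.
- **Influence is inferred.** The article reports no change in referral. The package targets system-level processes such as automated referrals, which are not deployed in the baseline year. One clinic is chosen because it does not routinely refer. This stands, and it is why no size can be given.
- **Any bias would be toward no effect, and this is a pilot without a power calculation.** True, and it protects against a false claim of improvement. It is less reassuring where the purpose is to obtain planning estimates. A reader might also infer that the future trial's control referral rate would be wrong, but the article does not say the pilot baseline will serve as that rate.
- **The year immediately before is the usual pre-post choice.** An older window controls secular change less well: with an April 2027 start, a window ending April 2023 would be four years old. This stands against replacing the stated year, but not against adding a second window.
- **Exact dates may sit in the full protocol.** That may be so. However, the article does fix the window relative to the intervention, and that anchoring creates the overlap.

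**Conclusion.** The point holds in limited form. At least 4 of the 12 baseline months fall during or after co-design. The minimum is 6 if the six-month co-design finishes first, and all 12 months are affected for any start from May 2025. No feasible baseline month precedes phase 1. This rests on reading the baseline as the 12 months immediately before rollout and on the package being available only after phase 2.

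That the baseline was actually raised is plausible but not shown, and neither the number of exposed pilot surgeons nor the size of any rise can be derived from the article. If it was raised, the reach and adoption differences shrink toward no effect. The absolute targets stand, because they do not use the baseline. This is an inexpensive improvement to a pre-post comparison, not a flaw that invalidates the pilot.

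**What to change.** In Phase 3, Study Design:

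1. State the planned start of rollout, and keep the 12 months immediately before it as a baseline window.
2. Add a second retrospective window with fixed calendar dates before study contact: the 12 months ending April 2023, or several earlier periods so that the referral trend is visible. The 12 months ending April 2024 would not serve, because they coincide with phase 1 and its surgeon interviews.
3. Report reach and adoption in the post period against both windows. If the two agree, there is little sign that the baseline had moved. If the later one is higher, say that study contact and secular change cannot be separated.
4. Where numbers allow, show results descriptively for surgeons who did and did not take part in phases 1 and 2. With 12 pilot surgeons, and ten referring surgeons invited in phase 1 alone, one group may be too small for more than a listing.
5. Add a sentence on prior study contact to the Limitations.

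The cost is additional chart abstraction of the kind already planned. The earlier window is more exposed to secular change, which is why both should be shown and neither dropped. Phase 3 still awaited ethics approval when the article was written, so the change could be made before it began.

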Experts and best practice guidelines recommend a pCGA for all older patients undergoing major surgery [15,31-33]. In prior work with the American College of Surgeons, an expert consensus conference of >50 stakeholder organizations generated national standards for the surgical care of older adults through the Geriatric Surgery Verification Program [34,35]. These standards include conducting a pCGA for older surgical patients. Defining the standards is a critical first step; however, this work is incomplete without generalizable implementation strategies applicable to real-world settings. A lack of evidence on how best to implement the pCGA in a variety of health systems has limited patient access to this intervention [36]. The few implementation studies that exist demonstrate challenges due to contextual factors (eg, misaligned incentives) and low fidelity to the intervention [36,37]. As a result, few programs use the pCGA for older surgical patients, and reach is limited to patients receiving care at large academic medical centers with significant resources. Thus, there is a critical need for novel, evidence-based strategies to promote the successful implementation of this intervention in a variety of health care settings. To address this gap, this study seeks to answer the research question “What implementation strategies will improve provider use (adoption) and patient access (reach) to the pCGA, while preserving effectiveness (fidelity) in academic and community medical settings?”

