#### Data Analysis

The aim of the pilot is to maximize reach and adoption while maintaining implementation fidelity before a full-scale implementation-effectiveness hybrid trial is conducted. The limited sample size will restrict our ability to evaluate differences in effectiveness outcomes such as mortality or morbidity; however, more proximal effectiveness estimates will be explored by abstracting short-term clinical outcomes (eg, medication changes at discharge). We will use exploratory measures to establish some preliminary point estimates for event rates and CIs within our sample for the purpose of planning a future study. As such, formal power calculations are not applicable to this pilot study. Recruitment data will inform the calculation of the reach, adoption, and maintenance outcomes. We will explore all RE-AIM outcomes for differences across underrepresented groups [69] (rural vs urban as determined by zip code, racial majority vs minority groups, men vs women vs other gender identities, and Hispanic vs non-Hispanic ethnicity). All data will be entered into Stata software (StataCorp LLC) for analysis. Data will be evaluated for accuracy and missingness. Descriptive univariate and bivariate analyses will be conducted, including chi-square tests for categorical data and 2-tailed *t* tests or Mann-Whitney *U* tests for continuous data as appropriate, with a cutoff of *P*<.05 for statistical significance.

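### Phase 3 compares reach with a historic baseline and makes no allowance for calendar time, so a background rise in pCGA referral would be counted as package effect; reach should be shown by month and clinic

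*Protocol article*

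**What the plan says.** The Phase 3 Study Design section describes the pilot, which has no control group, as follows: "We will conduct a pretest-posttest pilot study of the implementation package over 10 months, conducted at the clinic level at 2 busy academic medical center". The sites are two surgical clinics, chosen by "selecting one that does not routinely refer for pCGA in addition to one that does routinely refer". Both clinics get the package. On timing it says "We will collect baseline prepilot data via retrospective chart abstraction from the year before the intervention". For the period that follows launch it says "After an implementation rollout period of 2 months, postintervention data will be collected over 10 months". The hypothesis is "We hypothesize that a user-designed implementation package will improve the reach and adoption of the pCGA compared to the historic baseline".

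The Outcomes section makes reach and adoption the primary outcomes. Table 2 defines reach as referred patients over potentially eligible patients, with a target above 50% in each clinic. Under Maintenance it plans a look at trends at 6 and 12 months.

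The Phase 3 Data Analysis section says "Descriptive univariate and bivariate analyses will be conducted, including chi-square tests for categorical data". It also names t or Mann-Whitney tests for continuous outcomes, all "with a cutoff of *P*<.05 for statistical significance". It describes no concurrent series and no calendar-time term. The Limitations section does not mention secular trend.

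**The concern.** A before-after difference measures the package effect plus whatever would have happened anyway over the same interval. The article itself gives reasons why referral might be rising:

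- **Outside pressure.** The Background section says "Experts and best practice guidelines recommend a pCGA for all older patients undergoing major surgery", and the Dissemination Plans section notes that a national verification program requires the assessment.
- **The study's own activity.** Referring surgeons are interviewed in Phase 1. Surgeons and largely the same academic-center professionals take part in the Phase 2 co-design. Phase 1 opened in 2023 and Phase 2 in May 2024. Referral habits could shift before the package is launched.

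The crude change in reach is the evidence offered for the stated hypothesis, and it feeds the planning of a later stepped-wedge trial. If part of it is drift, the pilot overstates the package and the later trial is planned on an inflated figure. The Maintenance trends cannot help, because both time points fall after launch and say nothing about the slope before it.

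**Working it through.** The article gives no sample size, power or expected difference for reach, so there is no figure of its own to reproduce.

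**Step 1: distance between the periods.** The baseline is 12 months, rollout is 2 and post is 10. Taking the baseline year to end when rollout begins, the midpoints are 6 + 2 + 5 = 13 months apart. A linear drift of d points per month therefore adds 13 × d points to the crude difference:

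- d = 0.25: 3.25 points
- d = 0.5: 6.5 points
- d = 1.0: 13 points

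**Step 2: rejection rate with no package effect.** The article gives no baseline reach, eligible count or drift. I assume 20% baseline reach and 80, 120 or 200 eligible patients in the baseline year. The post period then has 10/12 of that: 67, 100 or 167. The test is the pooled two-proportion z test (equal to the uncorrected chi-square) at two-sided 5%:

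z = (p̂₂ − p̂₁) / √[p̄(1 − p̄)(1/n₁ + 1/n₂)]

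Summing the binomial probabilities exactly over all outcomes with |z| > 1.96, with p₁ = 0.20 and p₂ = 0.20 + 13d, gives:

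| Drift per month | p₂ | 80/67 | 120/100 | 200/167 |
|---|---|---|---|---|
| 0 | 20% | 5.3% | 5.1% | 4.9% |
| 0.25 points | 23.25% | 8.5% | 9.3% | 11.5% |
| 0.5 points | 26.5% | 16.7% | 21.2% | 31.1% |
| 1.0 point | 33% | 44.9% | 59.4% | 81.2% |

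With 40% baseline reach, the ranges are 7% to 10%, 13% to 24% and 35% to 70%. The pattern does not hinge on the 20% assumption.

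**Step 3: what a trend term would cost.** A simulation (2,000 runs per setting) used 25% baseline reach and 80, 120 or 240 eligible per year. It compared the pooled chi-square with a weighted linear regression of monthly proportions on month and a post-rollout step.

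| Setting | Method | 80 | 120 | 240 |
|---|---|---|---|---|
| 10-point drift, no effect | Pooled test | 26% | 38% | 65% |
| 10-point drift, no effect | Trend-adjusted | 5% | 5% | 5% |
| No drift, true 20-point step | Pooled test | 73% | 87% | 100% |
| No drift, true 20-point step | Trend-adjusted | 20% | 27% | 47% |

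With the true step, the average standard error of the adjusted estimate is 0.173, 0.141 and 0.100. The 95% interval is thus about ±34, ±28 and ±20 points (1.96 × SE). The adjustment removes the bias, but it is too imprecise to decide anything in a pilot of this size.

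**Step 4: is a monthly display workable?** The 40 pCGA patients per year in the Recruitment and Enrollment section (about 3.3 per month) are patients seen for the assessment, not the denominator of reach. With 80 to 200 eligible per year, the denominator is 80/12 = 6.7 to 200/12 = 16.7 per month over both clinics, or about 3 to 8 per clinic if they are equal in size. That supports a plot, with quarters as the fallback.

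**The case against.** The strongest reply is that this is a declared pilot. The Data Analysis section says formal power calculations do not apply, and the Future Directions section leaves the randomized test to a stepped-wedge trial. That stands, and it limits how much should be asked. It does not remove the issue, because the pilot still states a directional hypothesis against the baseline and a significance cutoff.

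A reader might go further than the document allows in four ways:

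- **That a single pooled chi-square is the fixed primary test of reach.** The tests are listed generically and none is tied to reach. A fuller analysis plan may say more. Any unadjusted before-after comparison has the same bias, however, and no other kind is named.
- **That this trial has a false-positive rate of 17% to 81%.** Those rates follow from assumed drift, baseline and volume. The Background section also says that few programs use the assessment despite the standards, which argues against assuming steep drift.
- **That drift alone would make the pilot look successful.** Under the 20% baseline, drift of 0.5 or 1.0 points per month leads to 26.5% or 33%, still short of the 50% target. The protection is partial: a clinic starting at 40% would reach 53% with 1.0 point per month, and one of the two clinics already refers routinely.
- **That a control is at hand and costs little.** The clinic that does not routinely refer receives the package, so it is not a comparator. Outside clinics would have to be added. Eligibility includes suspected cognitive or functional impairment, which a record query may not capture. Changes such as automated referral in the electronic record could also spill over to those clinics.

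**Conclusion.** The concern holds in limited form. The design and the named analyses cannot separate a background rise in referral from a package effect, the planned trend looks begin too late to help, and the limitation is not stated. The direction of the bias under rising referral is certain, but its size is not known. Over 13 months it is 3 to 13 points for drift of 0.25 to 1.0 points per month. The matching rejection rates run from about 9% to 81% against a nominal 5%, under the assumed 20% baseline and 80 to 200 eligible per year. At the low end of drift the inflation is small. The documents do not support calling the design invalid or requiring a control group. They do support a display of reach over time and more cautious wording. The point concerns reach only; adoption rests on 12 surgeons and cannot carry a time series.

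**What to change.** 1. Tabulate and plot reach by calendar month, or by quarter if counts are small, and by clinic, over the 12 baseline, 2 rollout and 10 post months. Report this beside the crude difference and the 50% target.
2. Give a logistic model with clinic, linear month and a post-rollout step as a supportive estimate with its confidence interval. State its low power, and do not make the conclusion depend on its P value.
3. Describe the before-after change as an association, and add secular trend to the limitations, including the study's own contact with referring surgeons before launch.
4. Treat non-pilot clinics as optional: only if eligible counts can be had without extra abstraction, and with contamination and the shared-trend assumption discussed.
5. Keep adoption descriptive.

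The cost is a little analysis and possibly a less favorable conclusion. The Chart Abstraction section lists the date of surgery, which can index the month; the date of the surgical consultation would be better for referral and may need adding. The Study Design section mentions data for the baseline year and the 10 post months, so counts for the 2 rollout months may also need adding. The intervention and patient enrollment do not change.
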